### Sample size

The primary outcome measure is the result of the medication review and patient counselling on the occurrence of DRPs. Based on previous studies it is estimated that the percentage of DRP in the patients of control pharmacists is 30%. It is estimated that the intervention reduces the number of preventable DRP with one third (33%). With a type 1 error of 0.05, a power of 80%, and a ration of one between both groups of patients, multilevel randomisation resulting in a loss of power of 15%, a total of 342 patients is needed to show a statistically significant difference. The estimated number of patients fulfilling the criteria and willing to participate is 4 per pharmacy per month. With an actual recruitment time of 6 months, and about 20 participating pharmacies, the number of 342 patients will be achieved.

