### Setting

The trial will be conducted in 23 community pharmacists in Amsterdam, Amstelveen, Hoofddorp and Diemen, the Netherlands. The medication review will be performed by a pharmacist in close collaboration with the general practitioner (GP). The patients will be counseled at home or in the pharmacy by a pharmacy technician.

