### Treatment allocation

Ten Pharmacotherapeutic Audit Meetings (PTAMs) will participate in the study. In the Netherlands general practitioners and pharmacists are organized in PTAMs. Within a PTAM pharmacists are randomized as a control or intervention pharmacist.

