### Analyses

Descriptive statistics (means ± SD or median and interquartile range in case of a skewed distribution) will be used to describe the whole study sample with regard to demographics, drug use and reason for previous hospital admission. The analyses will be conducted according to the intention-to-treat principle. To assess the impact of the intervention, multilevel linear and logistic regression analyses will be conducted to study differences in outcome measures between patients of the intervention and control pharmacies. Using multilevel analyses enables taking clustering of observations of participants receiving care from the same GP and for repeated measurements within one subject in account. Differences in changes between groups are measured with 95% confidence intervals. We will adjust data for possible confounders and effect modifiers (age, sex, ethnicity, level of education). Separate analyses of effect modifiers and mediators will be conducted in order to gain a better understanding which subgroups benefit most from the intervention. Confidence intervals of differences in costs between groups will be estimated using bootstrapping methods. (Bootstrapping statistics is a general method for performing statistical analyses without making strong parametric assumptions [32].

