There are several practical limitations associated with performing medication review. Detecting and solving drug related problems by health care workers such as community pharmacists is a time consuming process [35]. In order to make any changes in the drug regimen, the pharmacist has to contact the general practitioner first, which is time consuming. Furthermore, community pharmacists have to communicate the changes that are made with their patients. Because of their busy daily schedules, it may be possible that pharmacists do not find that medication review has a priority. Another major limitation is the possible bias in the detection and solving of DRPs by the different community pharmacists since all pharmacists have different experiences in performing a medication review. Some pharmacists will therefore identify more or less drug related problems than others, depending on the limited time. In addition, another limitation of the intervention is that the performance of CBT might differ between pharmacy technicians because of the interview skills they have. It is therefore difficult to decide whether all patients receive the same therapy sessions. We will try to reduce the differences between the pharmacy technicians, by using a structured interview protocol and motivational interviewing and problem solving treatment courses. A major strength is by combining medication review and CBT sessions can lead to a possible improvement of detection of drug related problems. The CBT sessions with patients discharged from the hospital will be helpful in detecting drug problems such as side effects and non-compliance, and thus lead to a better communication between the community pharmacy and patient.

A limitation of the study design is that there is no literature available that describes an evidence based method that can be used by pharmacists to report the quality of the pharmacotherapy or how to detect and solve drug related problems. However, we will apply in this study a method of prescription problems which we can test on feasibility and effectiveness. Strength of this study design is that it is a RCT.

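### The stated 80% power does not follow for 342 patients in total: the inputs give about 57% before clustering and about 51% after the plan's own 15% allowance, which is tied to no ICC or number of pharmacies

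*Protocol article*

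**What the plan says.** The Sample size section starts from "With a type 1 error of 0.05, a power of 80" per cent. It estimates that "the percentage of DRP in the patients of control pharmacists is 30" per cent and expects the intervention to cut this by one third. It adds "a ration of one between both groups of patients, multilevel randomisation resulting in a loss of power of 15" per cent and arrives at 342 patients overall. The Abstract, Design of the study and Study Population also give 342 as the size of the whole trial.

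The unit of allocation is the pharmacist: "Within a PTAM pharmacists are randomized as a control or intervention pharmacist" (Treatment allocation), with ten PTAMs taking part. On the number of clusters, Setting says "The trial will be conducted in 23 community pharmacists in Amsterdam, Amstelveen, Hoofddorp and Diemen, the Netherlands", while Sample size speaks of about 20 pharmacies. Under Analyses, "multilevel linear and logistic regression analyses will be conducted to study differences in outcome measures between patients of the intervention and control pharmacies". That section names the GP and repeated measurements as sources of clustering.

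**The concern.** Two things in the sample size paragraph do not fit the design described around it. First, the number that the inputs produce is a number per group, yet it is printed as the total. Second, clustering by pharmacy is covered by a constant of 15% that is linked to no ICC, no number of patients per pharmacy and no number of pharmacies, although the comparison rests on only 20 to 23 randomised units.

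The stated power tells a reader how to weigh a null result. A trial believed to have 80% power for a fall from 30% to 20%, but with nearer 50%, could have a non-significant result taken as evidence of no effect.

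**Working it through.** **Inputs from Sample size:** control 30%; one-third reduction, so 20%; alpha 0.05 (sidedness not stated, taken as two-sided); power 80%; ratio 1:1; clustering allowance 15%; 342 patients; about 20 pharmacies. **From Setting:** 23 pharmacies. **Assumed:** any ICC value, equal cluster sizes, and degrees of freedom equal to pharmacies minus 2.

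**1. Reproducing 342.** Variance term: 0.3×0.7 + 0.2×0.8 = 0.37.
n per group = (1.960 + 0.842)² × 0.37 / 0.10² = 7.849 × 37 = 290.4.
290.4 / 0.85 = 341.7, i.e. 342 **per group**.
Taking the 33% literally (20.1%) and multiplying by 1.15 gives 296.8 × 1.15 = 341.3, again per group. The pooled formula gives 294 per group, hence 338 (×1.15) or 346 (/0.85). None of the variants tried gives 342 as a total. The two-sided total before any allowance is 581 (unpooled) or 588 (pooled). Even a one-sided test without allowance needs about 458.

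**2. Power with 342 as the total (171 per group).** Non-centrality = 0.10 / √(0.37 × DE / 171), where DE is the design effect.
- DE = 1: 2.150, power 57.5% (57.0% with the pooled formula; 69% one-sided).
- DE = 1/0.85 = 1.176: 1.982, power 50.9%.
- Same DE, t reference on 23 − 2 = 21 df: 47.3%.

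Power falls as the ICC rises, so 57% is the ceiling and 80% is reached at no ICC.

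**3. What the 15% covers.** Solving 1 + (m − 1)×ICC = 1/0.85 for the ICC:
- 23 pharmacies, m = 342/23 = 14.9: ICC = 0.1765/13.9 = 0.0127.
- 20 pharmacies, m = 342/20 = 17.1: ICC = 0.1765/16.1 = 0.0110.

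**4. Power over assumed ICCs, 23 pharmacies, t on 21 df.**

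| ICC (assumed) | 342 in total: DE | Power | 342 per group (684 in total, m = 29.7): DE | Power |
|---|---|---|---|---|
| 0.01 | 1.139 | 48.5% | 1.287 | 72.4% |
| 0.02 | 1.277 | 44.2% | 1.575 | 63.7% |
| 0.05 | 1.693 | 35.1% | 2.437 | 46.0% |

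On the per-group reading, the plan's own allowance with a normal reference returns 80.0%, and 76.2% with t on 21 df. The small number of clusters alone therefore costs about 4 points.

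**5. Which reading fits the recruitment plan.** 4 per pharmacy per month × 6 months × 20 pharmacies = 480, or 552 with 23. Both exceed 342 and neither reaches 684.

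**The case against.** The article does recognise clustering and allows for it. A condensed article may leave the ICC and cluster size behind the 15% to the full protocol, and at 342 patients the allowance does cover an ICC of about 0.01. This stands, so the lack of a printed ICC is not by itself the fault. But no ICC in a fuller document could give 80% at 171 per group.

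A reader might infer that the 80% is sound provided the ICC is close to zero. That would be so only if 342 were per group. Every place that gives the number treats it as the whole trial, and the recruitment projection does not support 684.

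A reader might also infer a large ICC from the Discussion, where "Some pharmacists will therefore identify more or less drug related problems than others, depending on the limited time". That goes too far. Under Primary outcome measures, DRP prevalence at baseline and 12 months is determined by independent clinical pharmacologists, so differences in pharmacists' detection do not pass straight into the outcome. Differences in solving problems and in delivering the counselling may still do so, but the document quantifies neither.

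Nor do the documents support cutting the degrees of freedom to 12 for PTAM effects, since Analyses specifies none. Randomising within PTAMs and adjusting for covariates may recover some precision, but this cannot be quantified here. The pharmacy-level t reference is itself partly inferred, because Analyses compares pharmacies but does not name pharmacy as a clustering level. Finally, the planned 95% confidence intervals would show the imprecision of a null result, which limits the harm but does not correct the stated power.

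**Conclusion.** The point holds. For the printed total of 342, the stated inputs give about 57% power with no clustering and about 51% with the plan's own allowance, against 80% claimed. These two figures need no outside assumption beyond a two-sided test and reading the effect as 30% to 20%. Most of the gap comes from printing a per-group number as a total. That the per-group formula was the one used is an inference from the match of 341.7 to 342.

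The clustering part is smaller and depends on assumptions. The flat 15% covers an ICC of about 0.011 to 0.013 at 15 to 17 patients per pharmacy, and the small number of pharmacies costs about 4 further points. The range from 49% down to 35% depends on ICCs chosen for illustration, and the document does not show that the true ICC is high. Correcting 342 to a per-group figure would not settle this part: 72% at an ICC of 0.01 and 64% at 0.02 are still short of 80%.

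**What to change.** In the Sample size section:
- state whether 342 is a total or per group;
- replace the flat 15% by 1 + (m − 1)×ICC, with m the planned patients per pharmacy;
- use pharmacy-level degrees of freedom;
- in place of 80%, state the power for the planned numbers of patients and pharmacies over an ICC range, for example 0.01 to 0.05.

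This is a recalculation and a rewritten paragraph. Enrolment need not change, and the Discussion reports that inclusion has already taken place. The cost is a less favourable stated power.

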## Background

Drug related problems (DRPs) are events or circumstances involving drug therapy that actually or potentially interfere with desired health outcomes [1]. Examples of DRPs are contra-indications, interactions, adverse drug reactions (ADR) and inefficacy of treatment. Causes for these problems can be prescription errors, non-compliance with treatment and the specific effects of drugs in patients. Factors that increase the risk of DRPs are polypharmacy, co-morbidity, aging, non-adherence and lack of coordination between different treating physicians.

An increased number of prescribed drugs (polypharmacy) strongly increase the risk of DRP. Runciman found a correlation between increases in medication use and rates of adverse drug reactions associated with hospitalization [2]. Another recent review of studies of the effect of polypharmacy on the health state of elderly people has shown that multiple drug use is a strong predictor of hospitalisations, nursing home placement, death, hypoglycaemia, fractures, impaired mobility, pneumonia and malnutrition [3]. Furthermore, Leendert et al suggest that elderly people have a higher risk of hospitalisation caused by DRP, especially if they use have 4 or more co-morbidity [4].

Elderly people >75 year seem at higher risk for hospitalisation caused by DRP [2]. A study conducted in the Netherlands examined the occurrence of hospitalisations that were related to medication. This study showed 12.793 acute hospital admissions per year of which 714 admissions were medication related and 332 of these admissions were preventable. They calculated that 19.000 hospital admissions per year were related to medication and were preventable [4]. Specific risk factors were the number of prescribing physicians [5] and the number of diagnoses [6], the number and combination of several (inappropriate) drugs [6,7] and the use of inappropriate drugs [8-11].

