### Study Population

A total of 342 patients discharged from any department, except oncology and psychiatry, from any general and academic hospital in Amsterdam, Amstelveen, Hoofddorp and Diemen will be enrolled into the study. Patients 60 years and older, using five or more prescription-only chronic drugs when admitted to the hospital are considered eligible to participate into the study. The pharmacists will evaluate whether the patient uses 5 or more chronic drugs. Furthermore, to participate, the patients have to give written informed consent.

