### Outcome Measures

#### Primary outcome measures

Using a checklist including common drug problems, the prevalence of DRP in patients of control and intervention pharmacists will be determined at base-line and at 12 months by a team of independent clinical pharmacologists. The identification of drug problems by community pharmacist will be assessed on the basis of a structured interview of the patient and the medication overview of the patient registered in the pharmacy information and administration system.

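### The 342 patients stated as needed are also the 342 enrolled, with nothing left for loss over 12 months; full retention is necessary for 80% power but, with 342 in total, not sufficient

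*Protocol article*

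**What the plan says.** The Sample size section lists its inputs: type 1 error 0.05, power 80%, a DRP percentage of 30% among control patients, a reduction of one third, equal groups, and an allowance for the multilevel design. It concludes: "multilevel randomisation resulting in a loss of power of 15%, a total of 342 patients is needed to show a statistically significant difference".

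The same number is the enrolment target. Study Population reads "A total of 342 patients discharged from any department, except oncology and psychiatry" and goes on to say that these patients will be enrolled. The Abstract and Design of the study also give 342, the latter with one year of follow-up.

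Under Primary outcome measures, DRP prevalence "will be determined at base-line and at 12 months by a team of independent clinical pharmacologists". The second primary outcome, adherence, is a self-report scale. On this type of patient, the Background reports that "multiple drug use is a strong predictor of hospitalisations, nursing home placement, death".

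The article states no expected loss to follow-up and no inflation for it.

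**The concern.** A number needed for a given power is a number of patients with an outcome. When it is also the number recruited, any missing 12-month outcome takes the trial below its own requirement. Here some loss is foreseeable from the article itself: patients are 60 or older, on five or more chronic drugs and recently discharged from hospital, and the outcome is read a year later.

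What is at stake is how a null result on DRPs would be read. A reader who takes 80% at face value will give a non-significant difference more weight as evidence of no effect than the design can bear.

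**Working it through.** **Inputs.** From the Sample size section: alpha 0.05; power 80%; control proportion 0.30; reduction of one third, so 0.20 in the intervention group; ratio 1:1; 15% for the multilevel design. Two assumptions are needed. The test is taken as two-sided, because the article does not say. The 15% is taken as a loss of effective sample size, because that reproduces the printed figure.

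**Reproducing 342.** Two proportions, unpooled variance:

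n per group = (1.960 + 0.842)² × (0.30×0.70 + 0.20×0.80) / 0.10² = 290.4

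290.4 / 0.85 = 341.7, rounded up to 342.

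If 33% is taken literally (intervention proportion 0.201), n per group = 296.8, and 296.8 × 1.15 = 341.3, again rounded up to 342. By either route 342 is a *per-group* number and the whole 15% goes to clustering. No attrition margin is hidden in it.

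**Trying 342 as a total.** With pooled variance and a two-sided test, the inputs need 294 per group, or 588 in total, before clustering. After clustering the total is 677 (×1.15) to 692 (/0.85). A one-sided test needs 462 before clustering and 532 to 544 after it. None of the variants tried (pooled, unpooled, arcsine or continuity-corrected; one- or two-sided) gives 342 as a total.

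**Power after loss.** With n enrolled per group and a proportion d lost by 12 months:

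Power = Φ( 0.10 / √(0.37 / (0.85 × n × (1 − d))) − 1.96 )

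Example with 342 in total (n = 171) and d = 0: 0.85 × 171 = 145.35; √(0.37/145.35) = 0.05045; 0.10/0.05045 = 1.982; Φ(0.022) = 50.9%.

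| Assumed 12-month loss | 342 in total (171 per group) | 342 per group |
|---|---|---|
| 0% | 50.9% | 80.0% |
| 5% | 48.9% | 78.0% |
| 10% | 46.8% | 75.8% |
| 15% | 44.7% | 73.4% |
| 20% | 42.6% | 70.8% |
| 25% | 40.4% | 68.0% |

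**Sensitivity of the starting point.** With pooled variance, 342 in total and no loss gives 50.4% if the 15% is applied as ×0.85 and 51.3% if applied as /1.15. Ignoring clustering altogether it gives 57.0%. The choice of formula does not bring a total of 342 near 80%.

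**Evaluable numbers.** With 342 in total, 10% loss leaves 171 × 0.90 = 153.9 per group, and 20% leaves 171 × 0.80 = 136.8.

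**The case against.** **A dropout assumption may sit in the full protocol.** An article condenses, and an unstated assumption alone would be no finding. But this article prints every input together with the result, and the inputs use up the result. It then fixes enrolment at that same number. A dropout margin held elsewhere could not be part of this 342.

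**The loss rates are assumed.** This stands. The Background says that polypharmacy predicts death and nursing-home placement but gives no rate for this trial. If loss were 5%, the fall would be only about 2 points.

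**A missed visit may not mean a missing DRP outcome.** This stands in part. Independent pharmacologists determine prevalence with a checklist; the patient interview is mentioned in a separate sentence about identification by the community pharmacist, beside the pharmacy's medication overview; and control patients are visited once. Some patients who withdraw might still be assessable from pharmacy records. Patients who die are not, and self-reported adherence is lost with either. Intention-to-treat analysis does not recover an assessment that was never made.

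**Recruitment capacity exceeds the target.** The stated rates give 4 × 6 × 20 = 480 patients. The article uses this only to argue that 342 can be reached. It does not present the excess as a reserve, and the target stays at 342.

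**A stronger reading to avoid.** A reader might infer that 80% power would hold if every patient were retained, so that only attrition stands in the way. The article does not support this. It calls 342 a total throughout, and on its own inputs that total gives about 51% with no loss. Inflating the total to 342/0.90 = 380 for 10% loss would therefore not restore 80%.

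**Conclusion.** The point holds in this form: needed equals enrolled, no allowance for loss is left, and the unconditional 80% is not what the design delivers. At assumed losses of 10% to 20%, attrition costs about 4 to 8 points if 342 is the total (from 51% to 47% and 43%) and about 4 to 9 points if it is per group (from 80% to 76% and 71%).

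Attrition is the smaller of the two problems. Whether 342 is per group or in total moves power by about 29 points (80.0 − 50.9). The attrition gap would nevertheless remain if the total were corrected to 2 × 342 = 684.

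The conclusion rests on a two-sided test, on the one-third reduction applying to the full 30%, on the 15% acting as a loss of effective sample size, and on loss rates that the article does not supply.

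**What to change.** In the Sample size section:

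1. State whether 342 is per group or in total.
2. Separate the number enrolled from the number evaluable for DRPs at 12 months.
3. State an assumed 12-month loss (death plus withdrawal), with a range.
4. Replace the unconditional 80% with the power at the evaluable number per arm. If 342 is the total, compute this from 171 per arm; the per-group column must not be quoted for a trial of 342.

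Enrolment need not change, and the Discussion already reports inclusion as performed between January 2008 and March 2009. The cost is a short addition to one paragraph and a less favourable stated power. It restores no power, but it lets readers judge a null result correctly.

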## Methods/Design

### Design of the study

The study is designed as a randomized, controlled, intervention study involving 342 patients with a follow-up of one year. The intervention will be performed by community pharmacists. A flow-chart of the study is shown in Figure 2.

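### The stated sample-size inputs do not give a total of 342; with 342 patients in all, power for the planned effect is about 50–51%, not 80%

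*Protocol article*

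**What the plan says.** All inputs are in the Sample size section of the protocol article.

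- Control proportion: "it is estimated that the percentage of DRP in the patients of control pharmacists is 30" per cent.
- Effect: "It is estimated that the intervention reduces the number of preventable DRP with one third (33" per cent in the text).
- Error rates: "With a type 1 error of 0.05, a power of 80" per cent.
- Allocation: "a power of 80%, and a ration of one between both groups of patients".
- Clustering and result: "multilevel randomisation resulting in a loss of power of 15%, a total of 342 patients is needed to show a statistically significant difference".

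The article treats 342 as the size of the whole trial throughout. Design of the study describes an "intervention study involving 342 patients with a follow-up of one year". The Abstract and Study Population give the same number for total enrolment. The recruitment projection (4 per pharmacy per month, about 20 pharmacies, 6 months) is also set against 342 as the target.

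The endpoint is described under Primary outcome measures: "the prevalence of DRP in patients of control and intervention pharmacists will be determined at base-line and at 12 months". That sentence does not restrict the outcome to preventable problems. The test's sidedness is not given, but the Analyses section says "Differences in changes between groups are measured with 95% confidence intervals", which fits a two-sided test.

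**The concern.** Detecting 30% versus 20% with 80% power takes close to 300 patients per group even without clustering. A total of 342 is only 171 per group, and it is said to include a clustering allowance already. The inputs and the result therefore disagree on the face of the paragraph.

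The DRP outcome is the one on which the trial is sized. If readers take the 80% at face value, they will treat a non-significant result as fair evidence against the intervention. In fact the trial would have had about an even chance of missing the effect it was designed to find.

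**Working it through.** **Inputs.** p1 = 0.30 and p2 = 0.30 × (1 − 1/3) = 0.20 (0.201 if 33% is taken literally); α = 0.05; power 0.80; 1:1; 15% allowance, all from Sample size. Two-sided is my assumption, in line with the 95% intervals. The text does not say how the 15% is applied, so I used both n × 1.15 and n/0.85.

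**Step 1: size per group before the allowance (two-sided).**

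- Unpooled: n = (1.960 + 0.842)² × [p1(1−p1) + p2(1−p2)] / (p1−p2)² = 7.849 × (0.21 + 0.16) / 0.01 = 290.4.
- Pooled, with mean proportion 0.25: n = [1.960 × √(2 × 0.25 × 0.75) + 0.842 × √0.37]² / 0.01 = (1.2002 + 0.5119)² / 0.01 = 293.2.

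The total is already 581–586 before any clustering.

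**Step 2: with the 15% allowance.**

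| p2 | Formula | per group, × 1.15 | per group, /0.85 | total |
|---|---|---|---|---|
| 0.20 | unpooled | 334.0 | 341.7 | 668–683 |
| 0.20 | pooled | 337.1 | 344.9 | 674–690 |
| 0.201 | unpooled | 341.3 | 349.2 | 683–698 |
| 0.201 | pooled | 344.5 | 352.4 | 689–705 |

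A continuity correction raises these further.

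**Step 3: can 342 be reproduced?** As a per-group number, yes: 290.4/0.85 = 341.7, rounded up to 342. With 342 per group, power is 79.7% (effective n = 342 × 0.85 = 290.7) to 80.6% (342/1.15 = 297.4), which is the stated 80%.

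As a total that delivers 80% power, no. Even one-sided and with no allowance, the total is 458 (unpooled) to 462 (pooled). One-sided with the allowance it is 526–543.

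**Step 4: power with 171 per group, 30% versus 20%.** Power = Φ{[0.10 × √n − z × √0.375] / √0.37}, with z = 1.960 two-sided or 1.645 one-sided.

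| Effective n per group | Two-sided | One-sided |
|---|---|---|
| 171 (no clustering loss) | 57.0% | 68.9% |
| 171/1.15 = 148.7 | 51.3% | 63.6% |
| 171 × 0.85 = 145.4 | 50.4% | 62.8% |

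For example, with n = 148.7: (1.2194 − 1.2002)/0.6083 = 0.032, and Φ(0.032) = 0.513.

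**Step 5: effect detectable with 80% power, two-sided.** Solving the same expression for p2 gives 0.163 (× 1.15) or 0.162 (/0.85), relative reductions of 45.5% and 46.0%. With no clustering loss it is 0.172, a 43% reduction.

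**The case against.** **The per-group explanation is a reconstruction.** This stands. No formula is named, and other standard combinations give 334, 337, 345 or 352 per group. There is even a route to 342 in total: a one-sided test of 30% versus 20.1%, sized for 0.80 × 0.85 = 68% power, needs 170.5, so 171 per group. That route applies the loss in the wrong direction and does not deliver 80%, so it does not rescue the paragraph. It does show why the origin should be called probable and not certain.

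**The planned analysis may be more efficient than a two-proportion test.** Analyses plans multilevel models with repeated measurements and covariates, and DRPs are assessed at baseline. Adjustment can add power. As a rough linear approximation, adjustment multiplies the variance by 1 − ρ². Going from 293.2 to 148.7 effective patients per group needs 1 − ρ² = 148.7/293.2 = 0.507, so ρ is about 0.7. The article gives no correlation and claims no such gain. What stands is that 50–51% describes the unadjusted comparison, which is the one the Sample size section sets out.

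**Details belong in the full protocol.** That would answer an omission. Here inputs and result are both printed, and they disagree.

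**Stronger readings that the documents do not support.**

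- A reader might infer that the trial could never have recruited about 684. The projection of 4 × 20 × 6 = 480 holds only for the six-month plan. Setting names 23 community pharmacists, and the Discussion dates inclusion from January 2008 to March 2009.
- A reader might infer that power is far lower still because only preventable DRPs would fall. The article gives no preventable share of DRPs. The ratio in the Background concerns hospital admissions, and the 30% may itself already mean preventable DRPs. No power figure can be attached to this.
- A reader might add a loss for dropout. The article gives no rate, and a condensed article need not show such an allowance.

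**Conclusion.** The point holds. The stated total of 342 does not follow from the stated inputs, and 80% power is wrong as written. Two-sided, about 668–690 patients in total would be needed (up to about 705 with 33% taken literally).

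The 50–51% figure assumes a two-sided, unadjusted comparison of 30% with 20% and the 15% read as a sample-size inflation. Relaxing those assumptions moves it to 57% (no clustering loss) or 63–69% (one-sided), so the conclusion does not depend on how the ambiguous wording is read. That a per-group number was reported as the total is the likely explanation, but the error stands without it.

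The word "preventable" is a separate, smaller ambiguity. If the one-third reduction applies only to a subset of the DRPs counted in the endpoint, the difference on that endpoint is below 10 percentage points. The documents do not allow its size to be worked out.

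**What to change.** Rewrite the Sample size paragraph in one of two ways.

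1. **If 342 in total is the design:** state that 171 per group gives about 50–51% power for 30% versus 20% after the 15% allowance, or 80% power for a fall from 30% to about 16%. State that the test is two-sided and how the 15% is applied. Do not describe 342 in total as giving 80% power, and interpret a null result through the confidence interval for the difference.
2. **If 342 per group was intended:** correct the total in the Abstract, Design of the study, Study Population and Sample size, and redo the recruitment projection.

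In either case, add one sentence saying whether the 30% and the one-third reduction refer to all DRPs, as measured under Primary outcome measures, or only to preventable ones. This is a clarification of the assumption, not a change of endpoint.

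The first option costs only wording and a less favourable power statement. The Discussion reports that inclusion has already taken place, so no extra patients are asked for.
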